#### IV. List of abbreviations

---

| Abbreviations | Meaning                                                                           |
|----------------------|------------------------------------------------------------------------------------------|
| AE                   | Adverse Event                                                                            |
| BIA                  | Bioimpedance analysis                                                                    |
| BORG-Skala           | Scale for recording the subjective perception of exertion                                |
| CIPN                 | Chemotherapy-induced peripheral neuropathy                                               |
| EORTC QLQ-30         | European Organization for Research and Treatment of Cancer Quality of Life Questionnaire |
| GSLTPAQ              | Godin Leisure-Time Physical Activity Questionnaire                                       |
| HNSCC                | Head Neck Sarcoma Cell Cancer                                                            |
| IBIMA                | Institute of Biostatistics and Informatics in Medicine                                   |
| MMSE                 | Mini-Mental State Examination                                                            |
| OSHO                 | East German Haematology and Oncology Study Group e.V.                                    |
| POMS-F               | Profile of Moods States Fatigue                                                          |
| PRO                  | Patient Reported Outcome                                                                 |
| QoL                  | Quality of life                                                                          |
| ROM                  | Range of Motion                                                                          |
| SAE                  | Serious Adverse Event                                                                    |
| SPPB                 | Short Physical Performance Battery                                                       |
| TTB                  | Training diary                                                                           |
| UMR                  | Rostock University Medical Centre                                                        |
| VAS                  | Visual analogue scale                                                                    |

---

## **1. Introduction**

Worldwide, head and neck tumours (HNSCC) account for more than 685,000 cases with 375,000 deaths per year [1]. The Robert Koch Institute's forecast for 2020 shows around 20,000 new cases in Germany [2]. The therapeutic approaches are interdisciplinary due to the close collaboration between surgeons, radiotherapists, oncologists and other disciplines. Due to the location of the tumour and the intensive local therapy procedures, these patients often have a high chronic symptom burden. Many patients suffer from dysphonia, dysphagia, lymphoedema, weight loss, muscle atrophy, fatigue, chemotherapy-induced peripheral neuropathy (CIPN), pain and limited mobility, all of which affect quality of life (QoL) [3-6]. Therefore, interdisciplinary rehabilitation including treatment by physicians, psychologists, speech and movement therapists, nutritionists and occupational therapists is sought for HNSCC patients [7]. In general, rehabilitation aims to alleviate symptoms and compensate for dysfunction [3]. There is strong evidence for the benefits of exercise/physical activity in terms of body composition, muscular fitness, pain, flexibility and QoL for HNSCC patients [7-14]. Thus, exercise therapy is a key factor in patient well-being/outcome.

## **2. Aims of the study**

### **2.1. Rationale**

Many previous intervention studies with HNSCC patients have focused on standardised training during aftercare. This often involved the use of large exercise machines, which are expensive or require specialised training facilities. Furthermore, most studies focussed on a single training method (e.g. progressive strength training) that only focused on one symptom [8,10-13]. However, as most patients suffer from multiple impairments (movement restriction, pain, muscle atrophy, CIPN, fatigue), there is a need for more comprehensive holistic training programmes. In addition, surveys show that many HNSCC patients prefer to exercise at home, alone and at moderate intensity [15,16]. Consequently, HNSCC patients need an exercise programme that can be carried out at home, without large/expensive exercise equipment and taking into account their physical and mental impairments. Home training programmes also offer the advantage that theoretically all HNSCC patients can benefit from them. The training programmes can be tailored to the patient's individual needs and can be carried out flexibly in terms of time and space. They are also not limited in time like conventional rehabilitation programmes.

### **2.2. Own preliminary work**

An initial pilot study (A 2018-0153) was carried out at the UMR (ZIM III) in 2018/19 to develop and evaluate a home training programme for HNSCC without the use of large equipment. The first step was to put together a training programme with exercises that are suitable for independent training at home for HNSCC patients. This training programme was then evaluated by means of a 12-week training intervention with regard to patient compliance, the effects on physical functionality and QoL. In this study, the patients completed the training programme under supervision in small groups. The intervention comprised a total of 24 training sessions of 50 minutes each. On average, each session consisted of 15 minutes of warm-up/mobilisation (functional gymnastics), 10 minutes of coordination exercises, 15 minutes of strengthening exercises and 10 minutes of stretching/relaxation exercises. The training was carried out at low to medium intensity.

A total of 12 patients (6 male, 6 female,  $68 \pm 9$  years) were included in the study. Ten (83%) completed the study successfully. The attendance rate of the participants was 83% ( $20 \pm 3$  of 24 units). The functional tests showed various significant improvements in the range of motion (ROM) of the shoulder joints and the cervical spine. At the end of the intervention, all participants scored full marks in the Short Physical Performance Battery (SPPB, test includes balance, leg strength and walking speed). In the 6-minute walk test, patients covered an additional distance of 43 metres (+8.3%) after the intervention, whereby the subjective perception of exertion was significantly lower. In order to evaluate changes in QoL, the EORTC-QLQ-30 and EORTC H&N35 questionnaires were completed by the participants before and after the intervention. The analysis showed a trend towards an improvement in global QoL ( $p = 0.059$ ). The effect size corresponds to a medium effect ( $d = 0.626$ ). Positive changes were seen in three of the five functional scales of the EORTC-QLQ-30: physical function (+6.7 points,  $p = 0.008$ ,  $d = 1.077$ ), cognitive function (+48.3 points,  $p = 0.015$ ,  $d = 0.829$ ) and social function (+23.4 points,  $p = 0.031$ ,  $d = 0.604$ ). There were no statistically significant changes in the three symptom scales and six single items. In the symptom scales of the H&N35, only sexuality showed a significant improvement (-16.5 points,  $p = 0.031$ ,  $d = 0.928$ ). The "social contact" scale showed a tendency towards improvement (-8.6 points,  $p = 0.68$ ,  $d = -0.542$ ) [17,18].

The good compliance of the participants, the positive effects in terms of physical functionality and QoL provide an excellent basis for the transfer to a home training programme (home-based setting).

As part of the pilot study, an "Exercise manual for patients with mouth, jaw, face and neck tumours" was written (ISBN: 978-1099096082 ). It contains a total of 90 mobilisation, coordination, strengthening and stretching exercises for training at home. Videos of the exercises have been created to accompany the book. Both the book and the videos will be made available to the HNSCC patients participating in the study for independent practice at home.

### **2.3. Aim of the study**

The aim of this study is to evaluate the approach of individual home exercise training in HNSCC patients in a multicentre study with regard to its feasibility and its effects on different degrees of QoL.

The following primary and secondary outcomes are defined in order to adequately fulfil all objectives of the study:

### **2.4. Primary outcome**

Phase A (Feasibility)

Percentage of patients who complete the training intervention in a home-based setting over 12 weeks

Phase B (Quality of life)

Change in global QoL score (EORTC-QLQ-30) after a 12-week training intervention in a home-based setting

### **2.5. Secondary outcomes**

- Reasons for premature discontinuation of the 12-week training intervention
- Frequency and duration of training in the home-based setting on average per week (training volume)

- Medium-term change in QoL after a 12-week training intervention in the home-based setting
- Short-term change in mobility after a 12-week training intervention in the home-based setting
- Medium-term change in mobility after a 12-week training intervention in a home-based setting
- Short-term change in physical activity after a 12-week training intervention in a home-based setting
- Medium-term change in physical activity after a 12-week training intervention in a home-based setting
- Short-term change in balance ability/gait safety after a 12-week training intervention in a home-based setting
- Medium-term change in balance ability/gait safety after a 12-week training intervention in a home-based setting
- Short-term change in aerobic endurance capacity after a 12-week training intervention in a home-based setting
- Medium-term change in aerobic endurance capacity after a 12-week training intervention in a home-based setting
- Short-term changes in body composition after a 12-week training intervention in a home-based setting
- Medium-term changes in body composition after a 12-week training intervention in a home-based setting
- Correlations between the training volume during the 12-week training intervention and the effects with regard to QoL
- Correlations between the training volume during the 12-week training intervention and the effects on functionality
- Correlations between the training volume during the 12-week training intervention and the effects on body composition
- Relationships between daily activity and QoL
- Relationships between daily activity and functionality
- Correlations between daily activity and body composition
- Differences in the perception of the subjective effects of home training depending on gender

#### **3.3. Finanzierung**

The study is financed by grants from OSHO e.V. (start-up funding), partly from third-party funds from the project "Exercise therapy during and after cancer therapy - a project to improve quality of life" funded by the Krebsgesellschaft M-V e. V. and from third-party funds from Clinic III (haematology, oncology, palliative medicine).

## 4. Studiendurchführung

### 4.1. Allgemeines Studiendesign

The study is a multi-centre intervention study including a questionnaire and functionality assessment before and after completion of the intervention as well as a three-month follow-up (prospective longitudinal study). The study procedure is shown schematically in Fig. 1.

[figure not shown]

Fig. 1 Flowchart of the study process

Before recruiting the study participants at the individual sites, all therapists who are responsible for the initial and baseline diagnostics and for instructing the patient in the training programme are instructed in the questionnaires, measurements, protocols and exercise materials by a project employee at the UMR site. The therapists receive an overview of all tasks and documents that are to be handed out or completed at the respective examination times. During the entire study period, contact will be established between local therapists (doctors) and the UMR study management (by e-mail, telephone, video conference) if necessary (e.g. in case of questions).

Study participants are recruited locally at the locations of the participating centres/clinics/practices. If the inclusion/exclusion criteria are met, patient information is provided by a doctor/therapist or documentary. If the patient consents to the study, the initial diagnostics (pre-test) follows. This consists of two parts:

- Part 1 „Patient Reported Outcomes“ (PROs), and
- Part 2 Functional diagnostics.

The PROs include:

- a) Collection of disease-specific data regarding the tumour disease (treating/including physician)
- b) Recording of person-specific data (e.g. side effects)
- c) Recording of QoL using the EORTC QLQ-30 and EORTC H&N35 questionnaires
- d) Recording of physical activity using the GSLTPAQ questionnaire.

The functional diagnostics to determine the current actual state includes

- a) Measurement of the interdental distance at maximum mouth opening
- b) Measurement of the ROM of the shoulder joints and the cervical spine
- c) Measurement of the flexibility of the trunk using the "stand and reach test"
- d) Performance of the "Short Physical Performance Battery" (balance, walking speed, leg strength),
- e) Completion of the 6-minute walk test incl. BORG and CR-10 scale (perception of exertion and pain on exertion) and
- f) optionally carrying out a bioimpedance analysis (BIA).

**Patient-related:**

1. information and consent
2. pre examination
3. intervention: 12 weeks in a home-based setting after admission
4. post examination
5. follow-up examination after 3 months

**Study-related:**

Recruitment period: 12 months

Total duration of intervention incl. follow-up (data collection): 18 months

Total duration incl. final report: 21 months

|                                        |            |
|----------------------------------------|------------|
| Inclusion of first patient             | 01.01.2021 |
| Inclusion of last patient              | 31.12.2021 |
| End of examination of the last patient | 30.06.2022 |
| Integrated final report                | 30.09.2022 |

Table 1 Schedule of the study

## **4.2. Discussion of the study design**

Primarily, the short and medium-term effect of home training on the QoL of the patients is analysed. This means that the focus is on the intra-individual change in QoL between the time points pre (before the intervention), post (after the intervention) and follow-up. A control group is therefore not absolutely necessary.

## **4.3. Selection of the study population**

Only patients with a diagnosis coded with a final digit according to ICD: C00 - C14, C30 - C32 Malignant neoplasms of the lip, oral cavity, pharynx, upper respiratory tract ("head and neck tumours") are included. No persons in need of special protection are included.

In order to be able to assess the extent of training and the effects of home training in relation to gender, men and women should be included in the study in equal proportions if possible. However, it must be taken into account that three times as many men as women suffer from head and neck tumours [2], participation in the study is voluntary and depends, among other things, on the motivation of the patients as well as their state of health (inclusion and exclusion criteria).

### **4.3.1. Inclusion and exclusion criteria**

The recruitment of study participants is subject to certain inclusion and exclusion criteria, which are listed below:

**Inclusion criteria:**

- Age  $\geq$  18 years
- Patients with tumour disease in the mouth, jaw, face and neck area in follow-up care, at least 4 months after antineoplastic therapy (radiotherapy, surgery, chemotherapy or immunotherapy) or after completion of follow-up treatment

- able to walk
- proficiency in written and spoken German
- Patient must be physically and psychosocially able to participate in the study (medical assessment)

#### **Exclusion criteria:**

Patients who fulfil at least one of the following criteria will not be included in this study:

- non-consenting patients
- not fulfilling all inclusion criteria
- clinically relevant heart failure (NYHA III and IV),
- myocardial infarction within the last 4 weeks
- unstable angina pectoris
- higher-grade valvular disease (in the medical history),
- uncontrolled cardiac arrhythmia,
- chronic obstructive pulmonary disease (GOLD III and IV)
- peripheral arterial occlusive disease ( $\geq$ Stage III according to Fontaine)
- diseases that could seriously impair cognitive performance (e.g. dementia, stroke, Wernicke-Korsakoff syndrome)
- < 24 points on the Mini-Mental State Examination (MMSE)
- known alcohol dependency

#### **4.4. Subsequent exclusion of study participants**

Subsequent exclusion from the study takes place if a patient withdraws their consent.

#### **4.5. Intervention**

The training intervention takes place in a home-based setting over a period of 12 weeks. Patients are recommended to do the individually tailored exercises at least three days a week. The training duration per day should be 15 - 30 minutes. The patient is also recommended (in addition to training the exercises) to do endurance training 2 to 3 times a week for around 30 minutes, e.g. in the form of a walk, (Nordic) walking, cycling, swimming, dancing or similar. In order to avoid overloading through training, the BORG scale (see Appendix 6) is recommended for controlling the training. The Borg scale from 6 ("very, very easy") to 20 ("very, very strenuous") measures the individually perceived level of exertion during strength and endurance training. The optimum effort lies between the values 11 and 15.

The individual exercise programme is put together by sports scientists and/or physiotherapists based on the results of the initial diagnostics. Various mobilisation, coordination, strengthening and stretching exercises are used according to the patient's performance capacity/restrictions, which are believed to have positive effects on physical performance, functionality and QoL. All recommended exercises can be found in the "Exercise manual for patients with mouth, jaw, face and neck tumours", which the study participants receive. In addition, the selected exercises are saved as a video on a data carrier (DVD/stick), which the patient also receives. Depending on the feedback from the participants, it is possible to recommend further exercises after the first training sessions and make them available as video files (e.g. more demanding or more difficult exercises to improve performance). Materials such as elastic bands and exercise balls, which are required for the exercises, are provided to the patient free of charge.

The patient records their training in a training diary. Once a week, a local therapist calls the patient to enquire about the status quo and records this.

#### **4.6. Dokumentation**

The following questionnaires are used for the pre, post and follow-up examinations:

- Questionnaire for recording disease-specific data (Appendix 1)
- General questionnaire for the collection of personal data (only initial examination) (Appendix 2)
- EORTC-QLQ-30 and EORTC Module H&N 35: Recording of QoL (Appendix 3)
- Godin Leisure-Time Physical Activity Questionnaire (GSLTPAQ): Assessment of physical activity (Appendix 4)
- Final questionnaire: assessment of satisfaction with training programme and media/small equipment provided and supervision, current motivation of study participants with regard to continuation of the training programme (final examination only) (Appendix 5)

Various tests are used to objectively assess physical performance, functionality and body composition. These include:

- Profile of moods states fatigue scale (POMS-F): recording the current mood
- Measurement of the incisal edge difference (SKD): recording the mobility of the temporomandibular joint
- Range of motion (ROM) measurement of the cervical spine and shoulder joints using manual goniometers (objective measurements) and assessment of the extent of movement/restrictions to movement from the patient's and therapist's perspective (subjective information)
- Stand and reach test: assessment of the mobility of the back muscles
- SPPB: Test battery to assess balance ability, leg strength and walking speed
- 6-minute walking test incl. BORG and CR-10 scale: Assessment of aerobic endurance capacity, recording of the subjective feeling of exertion and subjective exertion pain
- Optional BIA: measurement of body composition

The total duration of the performance diagnostics is approximately 30 minutes. The results are documented in a protocol (Appendix 6).

The examinations listed are carried out both before (pre-test) and after the home-based intervention (post-test) as well as three months follow-up.

For all patients, the extent of training is documented in a TTB (Appendix 7). In the event of a drop-out, the reason for the cancellation is recorded.

The weekly telephone calls on the status quo (scope of training, motivation) are recorded in writing (Appendix 8).

##### **4.6.1. Data collection**

Both personal and disease-specific data are collected as part of this study. Information on QoL is collected by means of questionnaires. Performance diagnostics data and information on the intervention are also collected. The data collected in detail is summarised below:

Personal data: Gender, age, height, weight, marital status, school-leaving qualification, professional status, attendance of self-help group

Nicotine and alcohol consumption

Disease-specific data: Diagnosis incl. stage, year of diagnosis, medical treatment(s)

Data on sports history

Data on the intervention: Adverse events, motivation, satisfaction with support and documentation, amount of training, possible reason for and time of dropout

Questionnaires (pre/post/follow up): Information on QoL (EORTC QLQ-30, EORTC H&N35), physical activity (GSLTPAQ), assessment of current fatigue (POMS-F) on the day of the performance assessment

Functional diagnostics (pre/post/follow up): Inter-tooth distance at maximum mouth opening, range of motion (ROM) of the shoulder joints and cervical spine, flexibility of the trunk (stand and reach test), Short Physical Performance Battery (balance, walking speed, leg strength), 6-minute walk test (cardiovascular and pulmonary performance) incl. BORG and CR-10 scale (perception of exertion and pain on exertion), optional bioimpedance analysis (BIA)

#### **4.6.2. Data management**

The data is collected in the participating centres/clinics/practices and sent pseudonymised online via an encrypted connection to the UMR study centre. No personal data (e.g. name, date of birth, address, telephone number, etc.) will be sent. As a result, it is not possible to assign the data to a person, even if the wrong recipient is sent by mistake.

#### **4.6.3. Data analysis**

This study is a prospective longitudinal study. The data will be analysed by estimating the drop-out rate, descriptive statistics, correlation tests (correlation and regression analysis) and multifactorial methods for testing differences (e.g. analysis of variance with repeated measures). The data will be analysed in cooperation with the IBIMA of the UMR.

The evaluation with regard to phase I (feasibility) will take place after 25 patients have been included in the study. In addition, ad hoc analyses will be performed. In the case of rapid recruitment, this will be paused at 60 patients included in the study and, if necessary, continued depending on the results of the analyses.

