#### **6.1.3. Primary outcome**

This study consists of two phases.

Phase A (feasibility & quality of life, n = 25):

The hypothesis is tested that the proportion of patients completing the training intervention in the home-based setting over 12 weeks is  $\geq 70\%$ .

Phase B (quality of life, n = 35, total n = 60):

The hypothesis will be tested that the global QoL score (EORTC-QLQ-30) will increase significantly after a 12-week training intervention in the home-based setting.

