## **6.2. Determination of the sample size**

The case number calculation of phase I is based on the calculation that with  $n = 24$ , a 30% dropout rate can be estimated with an accuracy of  $\pm 18\%$  at a confidence level of  $1 - \alpha = .95$  (2-sided) (nQuery® Advisor 7.0 Statistical Solutions Ltd., Boston, MA, USA).

The sample size calculation for the trial (phase B) is based on the results of Felser et al. (28): global QoL pre:  $50.1 \pm 16.4$ ; post:  $58.3 \pm 16.2$ ;  $r = 0.618$  resulting in an effect size of 0.5755, which is detectable on a confidence level of  $1 - \alpha = .95$  (2-sided) with  $n = 42$  patients (nQuery® Advisor 7.0 Statistical Solutions Ltd., Boston, MA, USA). Assuming a 30% dropout rate based on our experience, a total of  $N = 60$  patients is required to be included in the study.

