## **8. Use of the data and publication**

### **8.1. Reports**

#### **8.1.1. Interims report**

An interim report will be prepared for 25 patients included in the study and submitted to the project leader and all investigators of the participating trial centres.

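### Recruitment may go past 60 depending on unnamed results and with no maximum N, so the two-sided 5% level of the primary QoL test is not protected as written

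*Protocol*

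**What the plan says.** Section 4.6.3 (Data analysis) plans a feasibility evaluation once 25 patients are included. It then adds: "In addition, ad hoc analyses will be performed". The next sentence covers rapid recruitment only: "this will be paused at 60 patients included in the study and, if necessary, continued depending on the results of the analyses". Neither sentence names an endpoint for the deciding analyses, a criterion for continuing, a maximum N or a significance level.

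Section 6.1.3 gives the total as fixed: "Phase B (quality of life, n = 35, total n = 60"). Its phase B hypothesis is a significant increase in the global QoL score after 12 weeks.

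Section 6.2 derives that total from one test. The pilot figures are described as "resulting in an effect size of 0.5755, which is detectable on a confidence level of" 0.95, two-sided, with 42 patients. The step to 60 is made with the words "Assuming a 30% dropout rate based on our experience".

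Section 6.1 lists ordinary paired tests against zero and mentions no sequential method.

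**The concern.** A sample size justified for one fixed analysis and a licence to add patients after seeing results do not fit together. Suppose QoL is tested at 60 enrolled, success is claimed if p < 0.05, and otherwise patients are added and everything is retested at 5%. The trial then has two chances of a false positive while reporting one nominal level. The p-value and confidence interval of the phase B primary outcome would overstate the evidence, and once the data have been seen this cannot be fully repaired. Maximum sample size and the rule for exceeding it are design features, and here the protocol itself states the rule.

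**Working it through.** **1. Reproduce the plan's own figure (inputs from section 6.2).**

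- Pre 50.1 ± 16.4, post 58.3 ± 16.2, r = 0.618; mean change 58.3 − 50.1 = 8.2.
- SD of the change = √(16.4² + 16.2² − 2 × 0.618 × 16.4 × 16.2) = √(268.96 + 262.44 − 328.38) = √203.02 = 14.25.
- Effect size = 8.2 / 14.25 = 0.5755, as stated.
- Paired t-test with noncentral t, two-sided alpha 0.05: n = 42 gives power 0.9536 and n = 41 gives 0.9490. So 42 is the smallest n with 95% power. The protocol does not state the power; at two-sided alpha 0.05, 80% would give 26 and 90% would give 34.
- Drop-out: 42 / (1 − 0.30) = 60, as stated.

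The stated 42 and 60 are therefore correct for exactly one analysis at two-sided 5%.

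**2. Apply the continuation clause to QoL.** Assumptions, none of which the protocol fixes:

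- 70% of enrolled patients are evaluable, following section 6.2, and the look at 60 has all 42 completers.
- There is one extension, to 70, 80, 90 or 120 enrolled: 0.7 × 70 = 49, 0.7 × 80 = 56, 0.7 × 90 = 63, 0.7 × 120 = 84 completers.
- The test is a two-sided t-test at 0.05 on all data at each look; success is claimed at the first significant result.

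Simulation of 400,000 trials with zero mean change:

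| Completers at the looks | Extend whenever p ≥ 0.05 | Extend only if 0.05 ≤ p < 0.20 |
|---|---|---|
| 42 only | 5.0% | – |
| 42, then 49 | 6.8% | 6.8% |
| 42, then 56 | 7.4% | – |
| 42, then 63 | 7.7% | 7.0% |
| 42, then 84 | 8.4% | 6.7% |

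**3. Cross-check without simulation.** Under the null, the two test statistics are approximately bivariate normal with correlation √(n₁/n₂). The chance that either exceeds 1.96 in absolute value is 6.8% for 42 then 49, 7.7% for 42 then 63, and 8.3% for 42 then 84, in agreement with the table.

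**4. Apply the clause to completion or drop-out only.** If patients are added because fewer than 42 have a post-test, and QoL is tested once at the end, there is one test at 5% and no material inflation.

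**5. Levels that would hold 5% overall.** A constant two-look boundary solved from the same bivariate normal gives a nominal two-sided level at each look of about 0.037 (42 then 49), 0.032 (42 then 63) or 0.029 (42 then 84).

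**The case against.** The case for leaving the text alone has several parts.

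- **The clause is conditional.** It applies only if recruitment is rapid, within a 12-month window (section 4.1), and may never be used. That stands. It limits when the problem can arise, but not what happens if it does.
- **The deciding analyses are not said to be QoL analyses.** Pausing at 60 and continuing if needed also fits a check on whether 42 completers will be reached, which would be harmless. This stands too, and is why a reader who infers that the 5% level has already been lost goes further than the text. However, the text does not restrict the decision to completion counts, and it adds undefined ad hoc analyses to the feasibility evaluation already placed at 25.
- **A statistical analysis plan may settle it.** It may set levels for planned looks. It does not remove a results-driven extension that the protocol itself permits.

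Two stronger readings are tempting. The first is a QoL test at 25 patients, inferred from the label "Phase A (feasibility & quality of life, n = 25"). Adding an efficacy test at about 18 completers (0.7 × 25 = 17.5) would give 8.6% even without an extension. But sections 2.4, 4.6.3 and 6.1 tie phase A and that look to feasibility and drop-out, and the only hypothesis under that label concerns completion. The label may mean only that these patients contribute QoL data to the total. Looking at QoL at 25 with no early claim, and going on to 60 regardless, would not inflate the final test.

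The second is that interim QoL results reach the people who coach and assess patients. Section 8.1.1 says "An interim report will be prepared for 25 patients included in the study and submitted to the project leader and all investigators" of the participating centres, but does not say that the report contains QoL. Neither reading is relied on here.

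**Conclusion.** The point holds in a limited form. Section 4.6.3 permits an open-ended, results-dependent extension of a trial that section 6.2 sizes for one two-sided 5% test. If the extension follows the QoL result, the real error is about 6.7% to 8.4%; if it follows completion or drop-out only, it stays at about 5%. The range rests on 70% evaluable patients, one extension to 49–84 completers, and a claim at the first significant look. The 5% level of the test is itself taken from the sample-size statement in section 6.2, since section 6.1 names no level. The inflation is moderate, but it affects the phase B primary result and is easily prevented before data are seen.

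**What to change.** In section 4.6.3, replace the continuation clause with text to this effect: recruitment beyond 60 may be resumed only to reach 42 patients with a post-test; the decision uses the count of post-tests and never QoL results; ad hoc analyses are exploratory and do not inform recruitment. State a maximum N. In section 6.1.3, add that the confirmatory QoL test is done once, after the last enrolled patient's post-test is due.

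If a results-based extension is really wanted, fix its size and the maximum N now and test at levels matched to that size: nominally about 0.037, 0.032 or 0.029 at each look for an extension to 49, 63 or 84 completers. A single level quoted without the extension size would not be enough.

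As a precaution, confine the 25-patient report in section 8.1.1 to feasibility and safety.

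The cost is a few sentences in three sections. The real price is that the sponsor gives up the freedom to extend after seeing QoL data, or pays for it with a stricter level at each look.
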